## 1. Background

Heart failure (HF) patients with limited response to Guideline-Directed Medical Therapy (GDMT) remain at high risk of morbidity, mortality, and adverse left ventricular remodeling (1,2). Randomized controlled trials (RCTs) have demonstrated a net clinical benefit of cardiac resynchronization therapy (CRT) in these patients, particularly in those with reduced ejection fraction and a wide QRS complex and left bundle branch block (LBBB) (3–5). However, 30–40% of the population receiving CRT fail to show clinical improvement with biventricular pacing, which is also a high-cost intervention from the Brazilian health system perspective (6–8).

As an alternative to conventional resynchronization—typically performed by implanting one lead in the right ventricular endocardium and a second lead in a coronary sinus branch—direct stimulation of the His-Purkinje system can be used, targeting either the His bundle or the left bundle branch (9–11). In His bundle pacing, the right ventricular lead is fixed near the apex of the Koch’s triangle, allowing for selective or non-selective capture of the His-Purkinje system. By engaging the heart’s native conduction system, this technique restores physiological ventricular activation and may prevent undesirable effects of conventional biventricular pacing, such as ventricular remodeling (12).

However, this technique has limitations. In many cases, the energy required to capture the His bundle is significantly higher compared to standard right ventricular pacing, potentially leading to rapid battery depletion—particularly in patients with intra- or infra-Hisian block or distal left bundle branch block. Moreover, the intrinsic ventricular activity measured by the device (R wave) may be of very low amplitude at the His bundle position, making pacemaker programming difficult (13,14). As an alternative to His bundle pacing, in 2017, Huang et al. described the first case of direct left bundle branch pacing in patients who were ineligible for His bundle pacing. In this approach, the right ventricular lead (usually the same used for His bundle pacing) is deeply fixed in the interventricular septum, reaching the subendocardial region of the left ventricle, enabling direct stimulation of the His-Purkinje system through activation of the left bundle branch (11).

Reference centers worldwide have reported success with conduction system pacing techniques compared to traditional procedures. However, data analysis for this technique in the Brazilian population is scarce. Cardiac resynchronization through physiological pacing—whether by His bundle or left bundle branch lead implantation—offers more physiological stimulation and substantially lower procedural and equipment costs, making it a promising alternative to biventricular CRT. Initial studies comparing conduction system pacing with biventricular cardiac resynchronization therapy (CRT) are underway in several countries. However, to date, no conduction system pacing study has had primary clinical endpoints such as mortality, hospitalization, or urgent heart failure visits.

## 2. Rationale

Conduction system pacing techniques have demonstrated procedural feasibility, reduced device-related costs, and clinical outcomes comparable to biventricular cardiac resynchronization therapy (CRT) in prior studies. However, there is a lack of prospective data evaluating their

effectiveness using clinically meaningful primary endpoints and health economic impact within the Brazilian health system (15–20).

### **3. Objectives**

#### **3.1. Primary Objective**

To assess whether conduction system pacing is non-inferior to biventricular cardiac resynchronization therapy in terms of heart failure–related net clinical outcomes over a 12-month follow-up period.

#### **3.2. Secondary Objectives**

The primary secondary objective is to assess the superiority of conduction system pacing over biventricular pacing with respect to total direct medical cost. Additional secondary objectives, evaluated over a 12-month follow-up period, aim to compare both treatment arms regarding: time to first event (composite of all-cause mortality, heart failure hospitalization, or urgent heart failure visits); change in left ventricular ejection fraction (LVEF); change in left ventricular end-diastolic volume; change in Kansas City Cardiomyopathy Questionnaire (KCCQ) Overall Summary Score (OSS); change in New York Heart Association (NYHA) functional class; change in six-minute walk test (6MWT) distance; change in B-type Natriuretic Peptide (BNP) and N-terminal pro-B-type Natriuretic Peptide (NT-proBNP) levels; change in EuroQol-5D (EQ-5D) score; change in QRS duration; and a hierarchical composite endpoint including death, heart failure hospitalization, urgent HF visits, and change in KCCQ Clinical Summary Score (CSS).

### **4. Methods**

#### **4.1. Design**

The PhysioSync-HF study is a randomized, controlled, multicenter, non-inferiority clinical trial, patient-blinded, with independent blinded adjudication of outcomes.

#### **4.2. Randomization**

Patient allocation will follow a 1:1 ratio using a randomization list generated by a blockrand function, which generates random assignments. The probability of allocation to either CRT group will be equal, and stratification will be performed by center using variable block sizes of 4 and 6 patients. The randomization list will be uploaded into the REDCap system, allowing participating sites to access the assigned treatment group only once all eligibility requirements are fulfilled. Randomization will be conducted independently by the Research Support Center of the coordinating site at Hospital Moinhos de Vento, ensuring confidentiality throughout the process.

#### **4.3. Eligibility**

#### 4.3.1. *Inclusion Criteria*

- Men and women aged  $\geq 18$  years
- Symptomatic congestive heart failure (NYHA class II–III), of ischemic or non-ischemic etiology
- Left ventricular ejection fraction (LVEF)  $\leq 35\%$  documented by imaging within the past 3 months (echocardiogram, cardiac MRI, nuclear imaging, or left ventriculography)
- Presence of left bundle branch block (LBBB) on electrocardiogram with QRS duration  $\geq 130$  ms
- Clinical indication for cardiac resynchronization therapy (CRT), as determined by the treating physician
- Clinically stable, as assessed by the treating physician
- Receiving maximally tolerated doses of angiotensin-converting enzyme inhibitors (ACEi), angiotensin receptor blockers (ARB), or angiotensin receptor–neprilysin inhibitors (ARNI); beta-blockers; and mineralocorticoid receptor antagonists

#### 4.3.2. *Exclusion Criteria*

- Heart failure classified as NYHA Class IV
- Life expectancy less than 12 months due to any condition
- Dementia or advanced cerebrovascular disease
- Planned to receive an implantable cardioverter-defibrillator (ICD) alone or with CRT
- Concurrent participation in another clinical trial involving cardiac pacing
- Pregnant women or women of childbearing potential (pre-menopausal, not using contraception)
- Inability to understand or sign the informed consent form

### 4.4. **Outcome Definitions and Measurements**

#### 4.4.1. *Primary Outcome*

The primary outcome, defined as “*heart failure–related net clinical outcome*,” will be assessed as an ordinal hierarchical composite outcome compared between groups using a proportional odds model. The ordinal scale will consist of the following (in hierarchical order):

1. All-cause mortality
2. Heart failure hospitalization
3. Urgent visit due to heart failure
4. Absolute change in left ventricular ejection fraction (LVEF) from baseline to 12-month follow-up, categorized into 5% intervals (e.g.,  $(-10, -5]$ ,  $(-5, 0]$ ,  $(0, +5]$ ,  $(+5, +10]$ ).

All-cause mortality was assigned the top-weighted category in the ordinal scale, and the greatest improvement in LVEF was assigned the lowest-weighted category. The study will assess whether conduction system pacing (CSP) is non-inferior to biventricular pacing (BiVP).

The non-inferiority margin will be defined as an upper bound of the 95% confidence interval (CI) for an odds ratio  $<1.2$ . If CSP reaches the non-inferiority bound, superiority will then be tested using the same proportional odds model with alpha preservation.

#### 4.4.2. Secondary

#### Outcomes

The main secondary outcome is the total direct medical cost associated with conduction system pacing compared with biventricular pacing. This comparison will be conducted in the modified intention-to-treat (mITT) population, and the time frame for the analysis will correspond to the duration of clinical trial follow-up. The additional secondary outcomes, assessed up to 12 months, include:

1. Time to death, heart failure hospitalization, or urgent visit for heart failure
2. Left ventricular ejection fraction (LVEF)
3. Left ventricular end-diastolic volume
4. Kansas City Cardiomyopathy Questionnaire – Overall Summary Score (KCCQ-OSS)
5. New York Heart Association (NYHA) functional class
6. 6-minute walk test (6MWT)
7. BNP or NT-proBNP levels
8. EuroQol-5D (EQ-5D)
9. QRS complex duration
10. Hierarchical composite outcome including death, heart failure hospitalization, urgent HF visit, and change in KCCQ Clinical Summary Score (CSS)

#### 4.4.3. Exploratory

#### Outcomes

Exploratory outcomes, assessed up to 12 months, include:

1. Left ventricular end-systolic volume
2. Proportion of patients with improvement in KCCQ-OSS by 5, 10, and 20 points
3. Index procedure duration (minutes)
4. Index procedure complication rate
5. Implant-related adverse events
6. Cost-effectiveness
7. Cost predictors
8. Budget impact
9. Outcomes assessed by cardiopulmonary exercise testing (CPET):
  - a. Peak  $\text{VO}_2$  (primary CPET outcome)
  - b. Percent predicted peak  $\text{VO}_2$
  - c.  $\text{VE}/\text{VCO}_2$  slope
  - d. Oxygen Uptake Efficiency Slope (OUES)
  - e. Resting end-tidal  $\text{CO}_2$  pressure ( $\text{PETCO}_2$ )
  - f. Heart rate recovery at 1 minute
  - g.  $T_{1/2}$  (time to 50% recovery of  $\text{VO}_2$ )

#### *4.4.4. Safety Outcomes*

Safety outcomes will be monitored throughout the entire study period, from initiation to completion. All adverse events (AEs) will be reported by the site investigators and categorized into three groups: AEs related to the index procedure, implant-related AEs, and o unrelated AEs.

#### *4.4.5. Adjudicated Outcomes*

The following expected outcomes will be reported and submitted for central adjudication: all deaths, to determine the cause of death; and all hospitalization and urgent visit events, to determine whether they were caused by heart failure. Events will be adjudicated based on the criteria detailed in the event adjudication protocol. Additionally, all echocardiograms (baseline, 6-month, and 12-month) will be submitted to an independent and blinded cardiovascular imaging core laboratory for assessment.

### **4.5. Sample Size**

Assuming an incidence of all-cause mortality of 6.2% in both groups (based on the RAFT trial, which reported 20.8% over 40 months via linear extrapolation), a 1-year heart failure hospitalization rate of 5.85% (RAFT: 19.5% over 40 months), and a 1-year urgent visit rate for heart failure of 0.5% (DAPA-HF: 0.5 events per 100 patient-years), along with an estimated absolute increase in left ventricular ejection fraction (LVEF) of 16% in the intervention group versus 14% in the control group (a conservative estimate based on the His-Alternative study, which showed increases of 16% and 13%, respectively), and a standard deviation of 6.5 (based on values of 6 and 7 in each group from the same study), a sample size of 304 patients would be required to achieve 80% statistical power with a two-sided alpha of 5% (one-sided alpha of 2.5%) and a non-inferiority odds ratio bound  $<1.2$  for the upper limit of the 95% confidence interval, accounting for a 5% loss to follow-up (assumed to be non-informative dropouts for the purposes of sample size calculation).

Due to slower-than-anticipated enrollment and the publication of a meta-analysis during the conduct of the PhysioSync-HF trial (Gin et al., Heart Rhythm, 2023) showing a greater improvement in LVEF in the intervention group (2.70–5.18%) than the originally assumed 2%, the Steering Committee decided to recalculate the original sample size.

The updated calculation assumed a 3% difference in LVEF improvement between groups, favoring the intervention arm. Although the originally anticipated difference based on the His-Alternative study was also 3%, a more conservative estimate of 2% had been used in the initial sample size calculation due to limited available data at the time. With the revised assumptions, the required sample size was reduced from 304 to 180 patients, while preserving the non-inferiority margin of OR less than 1.2 for the upper bound of the confidence interval and 80% statistical power. All simulations were performed using 10,000 repetitions, as detailed in Appendix A.

### **4.6. Interim Statistical Analyses**

Early termination based on efficacy is not planned for this study. The Data and Safety Monitoring Board (DSMB) will conduct safety analyses after approximately 25%, 50%, and 75% of the target sample size has been enrolled, and at least every six months thereafter. There is no

predefined criteria for early termination. Given that the trial does not incorporate interim analyses for efficacy or safety monitoring explicitly tied to the primary endpoint, no adjustment to the alpha level will be made for the final analysis of the primary endpoint.

#### **4.7. Timing of Final Analysis**

Final analyses for all endpoints will be conducted collectively at the end of the study, after a minimum 12-month follow-up for all randomized patients and after the data lock point.

#### **4.8. Timing of Outcome Assessments**

Following CRT implantation, all patients will be evaluated in person at a follow-up visit scheduled for 30 days  $\pm$  5 days post-index procedure to assess device parameters and identify potential procedure-related complications. The primary purpose of this visit is to ensure that the patient is in a stable clinical condition and to ensure that no lead dislodgement has occurred.

Subsequent follow-up will take place at 6 months  $\pm$  20 days through a second in-person visit at the enrolling center. During this visit, a comprehensive clinical evaluation will be conducted, including a reassessment of all baseline measures: laboratory tests (including BNP or NT-proBNP), electrocardiogram, echocardiogram, Kansas City Cardiomyopathy Questionnaire (KCCQ), EQ-5D, 6-minute walk test (6MWT), and cardiopulmonary exercise testing (for those enrolled in the sub-study). The follow-up period will be calculated from the date of the index procedure. For example, follow-up day 30 is defined as 30 calendar days after the index cardiac resynchronization therapy procedure (either conduction system or biventricular pacing).

The final visit will occur at 12 months  $\pm$  20 days, during which all previously described assessments will be repeated.

### **5. Analysis Populations**

#### **5.1. Intention-to-Treat (ITT)**

The intention-to-treat (ITT) population will include all randomized subjects, regardless of the treatment received or any violations of eligibility criteria.

#### **5.2. Modified Intention-to-Treat (mITT)**

The modified intention-to-treat (mITT) population will comprise all subjects in the ITT analysis who underwent the index procedure.

#### **5.3. Per-Protocol (PP)**

The per-protocol (PP) population will include all randomized subjects who fully adhered to the study protocol, received the treatment to which they were assigned, had no major protocol

violations (e.g., crossover to the opposite treatment arm during the study), and met all eligibility criteria at the time of randomization.

#### **5.4. Safety Population (As-Treated)**

The safety population will include all randomized subjects, analyzed according to the treatment actually received. That is, if a patient deviates from the protocol and receives the treatment opposite to their allocated arm, they will be analyzed within the group corresponding to the treatment received, regardless of initial randomization or any protocol deviations. For participants who crossed over, adverse events will be assigned to the treatment group corresponding to the therapy being received at the time of the event.

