### **6. Principles of Statistical Analysis**

The primary analysis will be conducted in the modified intention-to-treat (mITT) population. Safety outcomes will be primarily reported for the safety population, while the per-protocol (PP) population will be used for sensitivity analyses.

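### The primary safety comparison follows the device received, with none by randomized arm, so late complications of a failed implant attempt can be counted against the other technique

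*Combined protocol and SAP*

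**What the plan says.** Section 5.4 defines the set: "The safety population will include all randomized subjects, analyzed according to the treatment actually received". A patient given the opposite treatment is moved: "they will be analyzed within the group corresponding to the treatment received, regardless of initial randomization or any protocol deviations". A second rule, limited to participants who crossed over, places events by timing: "adverse events will be assigned to the treatment group corresponding to the therapy being received at the time of the event".

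Section 6 gives this set its role: "Safety outcomes will be primarily reported for the safety population". The only other use of analysis sets in this area is in Section 7.10, which repeats the efficacy analyses in the per-protocol and as-treated populations. No safety table by randomized arm is specified.

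Section 4.4.4 has adverse events "categorized into three groups: AEs related to the index procedure, implant-related AEs", plus a third group for unrelated events. Section 4.4.3 lists "Index procedure complication rate" and implant-related events as exploratory outcomes. Neither section says which arm carries an event when both techniques were tried in one patient. Section 4.8 places the visit that looks for procedural complications about 30 days after the index procedure.

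**The concern.** As-treated safety reporting suits treatments where exposure causes the harm. Here the attempt itself can cause harm, whether or not the device stays. A patient assigned to conduction system pacing (CSP) whose attempt fails, and who then receives biventricular pacing (BiVP), joins the BiVP group. An infection or haematoma found at the 30-day visit is then a BiVP event, even if the failed attempt caused it. The same holds in the other direction.

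Events during the attempt are unclear. Under the timing rule, something that happens before any biventricular device is in place is not literally a BiVP event. Under the grouping rule, the patient belongs to BiVP altogether. If the event stays with CSP while the patient moves, numerator and denominator no longer describe the same people.

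Crossover is foreseen: Section 5.3 uses it as the example of a major violation, and Section 7.5.1 uses it as an imputation covariate. At stake is whether the main safety table gives a fair comparison of two implant strategies. No planned table would show the reader if it did not.

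**Working it through.** The plan states no crossover rate, complication rate or safety power, so there is no figure to reproduce. Only the arm size comes from the documents: 90 per group (Appendix A). All rates and counts below are assumptions, chosen to show the mechanism.

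**Counts.** Suppose 9 of 90 CSP patients fail and receive BiVP, with 3 adverse events; the other 81 have 6 events; 90 BiVP patients have 7. A patient who switches is placed in the denominator of the device finally received.

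| Presentation | CSP | BiVP | Difference (points) |
|---|---|---|---|
| By randomized arm | 9/90 = 10.0% | 7/90 = 7.8% | +2.2 |
| As treated, 3 events to BiVP | 6/81 = 7.4% | 10/99 = 10.1% | -2.7 |
| As treated, 3 events to CSP | 9/81 = 11.1% | 7/99 = 7.1% | +4.0 |

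**General form, one-way crossover.** Let x be the share of CSP patients switched. Let pc be the risk after successful CSP, pf the risk after a failed attempt, and pb the risk in patients assigned to BiVP.

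- By randomized arm: (1-x)pc + x·pf - pb = (pc - pb) + x(pf - pc).
- As treated, all failed-attempt events to BiVP: pc - (pb + x·pf)/(1+x) = [(pc - pb) - x(pf - pc)]/(1+x).

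With pf > pc, the two differ in sign exactly when |pc - pb| < x(pf - pc).

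| x | pc | pb | pf | pc - pb, absolute | x(pf - pc) | By arm | As treated |
|---|---|---|---|---|---|---|---|
| 5% | 8% | 8% | 20% | 0 | 0.6 | +0.6 | -0.6 |
| 10% | 8% | 8% | 20% | 0 | 1.2 | +1.2 | -1.1 |
| 20% | 8% | 8% | 20% | 0 | 2.4 | +2.4 | -2.0 |
| 20% | 10% | 8% | 30% | 2.0 | 4.0 | +6.0 | -1.7 |
| 10% | 10% | 5% | 20% | 5.0 | 1.0 | +6.0 | +3.6 |
| 10% | 6% | 8% | 20% | 2.0 | 1.4 | -0.6 | -3.1 |

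The last four columns are in percentage points. The first four rows reverse. In the fifth the excess only shrinks, and in the sixth an apparent CSP advantage is enlarged.

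**Varying the attribution.** Let q be the share of failed-attempt events charged to CSP. The as-treated difference is then pc + q·x·pf/(1-x) - [pb + (1-q)x·pf]/(1+x). With x = 10%, pc = pb = 8% and pf = 20%, the by-arm difference is +1.2. As treated:

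- q = 0: -1.1
- q = 0.25: -0.1
- q = 0.5: +0.9
- q = 0.75: +1.9
- q = 1: +2.9

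So the same data can understate, reverse or overstate the difference, depending on a choice that Section 5.4 does not make.

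**The case against.** A reader might infer that all complications of a failed CSP attempt are charged to BiVP, that the rule always favours the technique that fails more often, or that the safety comparison will reverse. The documents support none of these. The timing rule covers only participants who crossed over, and it clearly moves only events after the switch. If events during the attempt stay with CSP, the distortion runs against CSP (+4.0 versus +2.2 in the counts above). Nor is reversal in a worked example strong evidence: with pc = pb, the condition is met for any x above zero once all failed-attempt events go to BiVP.

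The shifts are also small beside sampling error. For 6/81 versus 10/99, the standard error is √(0.074×0.926/81 + 0.101×0.899/99) ≈ 4.2 points, against a difference of 2.7. No safety hypothesis or margin is set, the procedural outcomes are exploratory, and the wording of Section 6 does not forbid a further table by arm.

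All of this stands, and it limits the severity. It does not remove the defect. The direction of a descriptive safety result should not depend on an unwritten rule, and a table that is merely allowed is not a planned one.

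**Conclusion.** The point holds as a should-fix. Followed as written, the plan moves late complications of a failed attempt to the other technique, leaves events during the attempt without a clear home, and specifies no by-arm safety table that would reveal the effect.

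The size cannot be fixed from the documents. Under the assumed rates, the as-treated difference departs from the by-arm difference by anything from a fraction of a point (+0.9 versus +1.2) to 7.7 points (+6.0 versus -1.7). Reversal needs similar risks in the two arms and most failed-attempt events charged to the final device. These figures assume one-way crossover and a higher risk after a failed attempt.

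The primary outcome and the main secondary cost outcome are analysed in the modified intention-to-treat (mITT) population (Sections 6 and 7.5.1), so this rule does not touch them.

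A smaller gap sits beside it. The safety set takes in everyone randomized, but a patient who never had a procedure, whom Section 5.2 leaves out of mITT, has no treatment received to be grouped by.

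**What to change.** Before adverse events are compared between arms:

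1. Add a table of adverse events, in particular index-procedure and implant-related events, in the mITT population by randomized arm, with numerator and denominator both by allocation. Present it at least alongside the as-treated table, and preferably ahead of it.
2. Keep the as-treated table as supportive. State in it how events during and after a failed attempt are attributed.
3. Limit the as-treated table to patients who had a procedure.

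Attributing events to the first strategy attempted is not advised here. The documents do not show that the attempted strategy is recorded, and combining it with a by-arm denominator would bring back a mismatch for patients taken straight to the other technique.

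The cost is SAP wording and one extra table; the allocation is already held (Section 4.2), so no new data are needed. The drawback is that a by-arm table mixes device effects when crossover occurs, which is why the as-treated table stays.
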